### 2.10. Data management

All the data collected in the baseline screening, or at time points during the study period, will be recorded on the day participant visit the clinic. The embryological-related data will be recorded each day from the oocyte retrieval to the embryo transfer. Follow-up in the study will continue until 1 year after randomization, or during which time a live birth is achieved or all embryos are transferred.

Researchers at each reproductive center will undergo data management training to ensure the data reliability and privacy of participants. The data will be collected in compliance with the prespecified standard operating procedure. Collected data will be uniformly managed by the database of the Reproductive Center of Shandong University of Traditional Chinese Medicine. All protocol deviations or modification results should be recorded in detail and properly documented. The data will be collected, entered, and coded into a standard case report form (CRF) using the double-entry method. CRFs will be kept in locked filing cabinets. And the electronic CRFs will be kept in computers with passwords and access will only be allowed to the principal researchers. All data will be de-identified by CRFs and will be kept for 5 years. After that period, the electronic data will be removed.

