### 2.6. Randomization, allocation, and blinding

Randomization and allocation will start on day 2 or 3 of the previous menstrual cycle before IVF. Eligible women will be stratified by AFC (<5 or ≥5) and randomized within the 2 strata. All participants will be randomly assigned to either the EZTG group or the placebo group in a 1:1 ratio. Randomization will be completed by software (R 4.0.0, R Foundation for Statistical Computing, Vienna, Austria), and different-sized block groups of 2, 4, 6 will be applied. Random number tables will be provided by statistical professionals not involved in the rest of the study and the number will be sealed into brown envelopes. Then the group allocation will be accomplished by opening envelopes sequentially in the order in which patients were recruited.

A double-blind study design will be applied to enhance the quality of the study evidence. Both medications (EZTG granules and placebo) will be prepared in a manner that they will appear similar in appearance, flavor, and smell. Clinicians and patients will not be able to distinguish the difference between groups. The outcome assessment and data analysis will also be conducted in blinding. When the clinical trial is over, the final blind-break process is performed by authorized researchers.

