#### 2.7.3. COS and oocytes retrieval.

Participants will be assessed again for eligibility on day 2 or 3 of the IVF cycle. The participants will also receive hormonal and ultrasound assessments to ensure the feasibility of COS.

Eligible participants will be administrated COS with a Gonadotrophin-releasing hormone antagonist protocol on day 2 or 3 of the menstrual cycle and given recombinant follicle stimulating hormone (Gonal-F, Merck Serono, Switzerland). The starting dose of rFSH will be in a range between 150–225 IU/day, based on the individual baseline characteristics. The COS process will be individualized, and the follow-up dose of rFSH will be adjusted according to the ovarian response during COS every 2 or 3 days. On day 5 or 6 of the ovarian stimulation, gonadotrophin releasing hormone-antagonist (cetrorelix acetate, Cetrotide; Merck Serono, Germany) will be initiated. When more than 2 follicles are at least 18 mm, 250 mg of recombinant human chorionic gonadotrophin will be administered to trigger the final follicular maturation. After 35 to 37 hours, transvaginal ultrasound-guided aspiration is performed. Intracytoplasmic sperm injection will only be performed in cases of severe male factors of infertility.

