### 2.8. Outcomes

#### 2.8.1. Efficacy outcomes.

The primary outcome is the number of oocytes retrieved per COS cycle.

The following secondary outcomes will also be evaluated as secondary outcomes:

Symptom rating scores of kidney qi-yin deficiency syndrome after treatment (The symptom rating scales is shown in Table 3).Difference in rating scores of kidney qi-yin deficiency syndrome before and after treatment.Average daily dose of gonadotropin per COS cycle.Total gonadotropin dose and duration of ovarian stimulation per COS cycle.Cycle cancelation rate per COS cycle. Cycle cancelation is defined as a cycle canceled before obtaining at least 1 viable embryo for any reason.Good quality embryos rate per embryo. A good quality embryo is defined as an embryo that is graded as 6-cell grade 2 (6CII) or better or blastocyst.Embryo implantation rate per embryo, defined as the number of gestation sacs detected divided by the number of embryos transferred.Clinical pregnancy rate per patient, defined as the number of women with identified clinical pregnancies divided by the number of patients randomized to a specific group. Clinical pregnancy is confirmed when 1 or more gestational sacs are detected on transvaginal ultrasound assessment.Early miscarriage rate per patient, defined as the percentage of participants with loss of a diagnosed clinical pregnancy before 12 weeks gestation to the total patients randomized.CLBR per patient, defined as the proportion of deliveries with at least 1 live birth per started cycle or oocyte aspiration, including all fresh and/or frozen embryo transfers until 1 delivery with a live birth or until all embryos were used (within 1 year after randomization).

**Table 3 T3:** Symptom rating scales of kidney qi-yin deficiency syndrome.

Symptoms	Characteristics and severity of the symptoms	Score
The color and quality of the menstruation	The color of the blood is dark red and the quality is thin and watery	5
	The color of the blood is dark red or the quality is thin and watery	3
	Normal color and quality	0
The waist and knees are sour and powerless, or pain in the heels	Severe discomfort that interferes with daily life	6
	Moderate discomfort	4
	Mild discomfort	2
	No obvious discomfort	0
Dizziness and tinnitus	Severe, occurs constantly and interferes with daily life	6
	Moderate, occurs frequently	4
	Mild, occurs occasionally	2
	Not obvious	0
Mental exhaustion	Severe, occurs constantly and interferes with daily life	6

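### Cumulative live birth rate: the per-patient label is not matched by the denominator, and the end of follow-up and the one-year limit are worded so that births could be lost

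*Protocol article*

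**What the plan says.** CLBR is the last secondary outcome in section 2.8.1: "CLBR per patient, defined as the proportion of deliveries with at least 1 live birth per started cycle or oocyte aspiration". It counts transfers "including all fresh and/or frozen embryo transfers until 1 delivery with a live birth or until all embryos were used (within 1 year after randomization" (the parenthesis closes there). In the same list, the clinical pregnancy rate is "divided by the number of patients randomized to a specific group", and early miscarriage also uses all women randomised. Section 2.9.2 applies intention-to-treat analysis to the secondary outcomes.

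Section 2.10 gives the follow-up rule: follow-up continues "until 1 year after randomization, or during which time a live birth is achieved or all embryos are transferred". The Discussion describes follow-up simply as one year from randomisation and presents this, with CLBR per patient, as an improvement on the pilot study.

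The clock starts early. Section 2.6 says: "Randomization and allocation will start on day 2 or 3 of the previous menstrual cycle before IVF". Stimulation begins a cycle later, under a "Gonadotrophin-releasing hormone antagonist protocol on day 2 or 3 of the menstrual cycle" (section 2.7.3).

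**The concern.** Three rules that fix the CLBR are stated, and each is stated badly.

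1. **Denominator.** A rate labelled per patient is defined on two other units. Women who are randomised but never start stimulation fall out of the first. Women cancelled before retrieval also fall out of the second. Both losses occur after randomisation, so neither rate is an intention-to-treat rate.
2. **End of follow-up.** If follow-up may stop once all embryos are transferred, the result of that last transfer lies outside it. Section 2.8.1 needs an ultrasound, a 12-week miscarriage check and a delivery, all of which come later.
3. **One-year limit.** The text does not say what must happen within the year. If it is the delivery, late frozen transfers cannot contribute. If the treatment works by giving more oocytes and so more embryos to use later, those are the transfers at risk.

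**Working it through.** **The plan's own figure.** The article gives no expected CLBR and no power for it. Its only sample-size figure is 480 for the primary outcome. With a difference of 1, SD 3, two-sided 5% and 90% power, the normal formula gives 190 per arm. Then 190/0.8 = 237.5, rounded up to 238, or 476 in total. The t-test version gives 191, then 239, or 478 in total. Both agree closely with 480, and nothing below touches that number.

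**Denominator.** Section 2.5 removes women for pregnancy before the IVF cycle, poor compliance or adverse reactions, and section 2.7.3 re-checks eligibility at the start of the IVF cycle. Losses between randomisation and a started cycle are therefore foreseeable. As an illustration, assume that all of the planned 20% dropout falls in that interval:

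- Starters per arm: 240 × 0.8 = 192.
- At an assumed 15% per started cycle: 192 × 0.15 = 28.8 expected births, and 28.8/240 = 12% per woman randomised.
- Assumed rates of 10% and 20% become 8% and 16%.
- With 15% per started cycle, early dropout of 10% gives 13.5% per woman randomised, and 25% gives 11.3%.
- If losses differ by arm, the comparison itself moves. With 28.8 births in each arm but 192 starters in one and 216 in the other, the rates are 15.0% and 28.8/216 = 13.3% per started cycle, against 12% in both arms per woman randomised.

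**End of follow-up.** Birth occurs 7 × gestational weeks − 14 days after retrieval, or after the equivalent day for a frozen embryo: 266 days at 40 weeks and 245 at 37 weeks. Transfer is on day 3 or 5 (section 2.7.4). Transfer to birth is therefore between 245 − 5 = 240 days (about 34 weeks) and 266 − 3 = 263 days (about 38 weeks). On the literal rule, follow-up would end that long before a term birth from the final transfer. Section 2.4.1 lists fewer than 3 oocytes at a previous retrieval among its criteria, and section 2.7.4 allows 2 embryos per transfer, so the final transfer may be the only one.

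**One-year limit, if it applies to deliveries.** Days are counted from randomisation. Cycle length (24 to 35 days), stimulation length (8 to 14 days) and birth at 37 to 40 weeks are assumptions; the article does not give them.

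- Retrieval day = cycle length + stimulation + 2: from 24 + 8 + 2 = 34 to 35 + 14 + 2 = 51.
- Birth after fresh transfer: from 34 + 245 = 279 to 51 + 266 = 317. At least 365 − 317 = 48 days remain.
- Births at 40 weeks with 28-day cycles and retrieval on about day 40:

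| Transfer | Calculation | Day of birth |
|---|---|---|
| Fresh | 40 + 266 | 306 |
| Frozen, next cycle | 68 + 266 | 334 |
| Frozen, one cycle later | 96 + 266 | 362 |
| Frozen, the cycle after that | 124 + 266 | 390 |

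- Range for a frozen transfer in the next cycle: 34 + 24 + 266 = 324 to 51 + 35 + 266 = 352, inside the year throughout. One cycle later: 34 + 48 + 266 = 348 to 51 + 70 + 266 = 387, so this one depends on cycle length.
- Allowing time for a pregnancy test and the return of menses after a failed fresh transfer (retrieval on day 41), births at 37 to 40 weeks fall on days 321–342 after a frozen transfer in the next cycle, 349–370 with one rest cycle, and 356–377 after a second frozen transfer.
- Latest transfer that can count at 40 weeks: 365 − 266 = 99, plus 3 or 5 days of culture, so day 102 or 104. At 37 weeks: 365 − 245 = 120, so day 123 or 125.

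**The case against.** A reader might infer that follow-up really will stop on transfer day and that most births will be missed. The documents do not support this. Section 2.7.4 continues luteal support to 10 weeks of gestation and stops it on a pregnancy test or ultrasound. Section 2.8.1 follows women to a delivery, and the Discussion speaks of one year. All of these imply contact after transfer, and the visit timetable (Table 1) is not legible here. What stands is a conflict of wording in the follow-up rule that ten centres have to apply.

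A reader might also infer that the one-year limit by itself cuts off the births that CLBR should count. It does not. Births after fresh transfer and after a frozen transfer in the next cycle fit within the year, and the limit may apply only to the use of embryos. Nor is it true that later transfers count only if the birth is preterm: a 37-week birth fits for transfers up to about day 123 to 125.

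A bias toward no effect is conditional. It needs the delivery reading, enough late frozen transfers (the article gives no frequency), and a benefit that comes through surplus embryos. The pilot's only reported clinical difference was in high-quality embryos, which could act on first transfers, and those are captured.

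On the denominator, with one study cycle per woman, started cycles differ from randomised women only by those who never start. That limits the size of the discrepancy, but it leaves the text with two units that both contradict its label.

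**Conclusion.** The point holds as a defect in the definition and follow-up of a secondary outcome.

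- **Denominator:** a plain contradiction in the text, resting on no assumption. The shift in level is, for example, from 15% to 12% if all of the planned 20% dropout precedes the IVF cycle. It distorts the comparison between arms if losses differ.
- **End of follow-up:** the literal rule conflicts with the outcomes in 2.8.1 and the one-year follow-up in the Discussion. This has to be reconciled; it does not show that births will be lost.
- **One-year limit:** ambiguous. If it applies to deliveries, births from transfers after about day 102 (40 weeks) to day 125 (37 weeks) are lost. How many women that concerns cannot be worked out from the article. Any dilution of a CLBR benefit is possible rather than established.

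The primary outcome and N = 480 are unaffected.

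**What to change.** - **Section 2.8.1:** define CLBR as the number of women with at least one live birth from any fresh or frozen transfer of study-cycle embryos performed within one year of randomisation, divided by all women randomised to the group. Delete the reference to started cycles and aspirations.
- **One-year limit:** state that it applies to the date of transfer, and follow each pregnancy from an included transfer to its outcome, whatever the delivery date.
- **Section 2.10:** end follow-up at live birth, or when the outcome of the last included transfer is known.

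Whether a conception before the IVF cycle counts as an event is a separate decision, and this change does not depend on it.

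The cost is wording, plus telephone or record follow-up of pregnancies that are ongoing at one year. A transfer on day 365 leads to a 40-week birth up to 263 days later (365 + 263 = day 628), so final CLBR data may come up to about 9 months later. Section 2.6 breaks the blind when the trial is over, so the plan should also state whether unblinding and reporting of the primary outcome wait for CLBR or are staged.

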### 2.11. Trial monitoring

A trial monitoring committee (TMC) has been established, including principal researchers in each reproductive center. The TMC is responsible for data monitoring, adverse event assessment, regulation of the study process monthly, the interim analysis, and the decision on terminating the study or not.

### 2.12. Ethics and consent to participate

The ethical approvals of the study have been obtained from all participating reproductive centers. EZTG formula has been used in some reproductive centers as one of the conventional treatments for infertility and applied as a complementary treatment in ART. So far, there are no adverse events related to EZTG reported. In the study, all of the medications used in IVF cycles are regular and comply with the routines. The intensity of adverse events will be categorized as light, moderate, serious, and suspected unexpected serious adverse events. Serious adverse events should be reported to the TMC immediately. Meanwhile, the blind-break process will be performed, and the trials will be discontinued. If the relationship with the trial is confirmed, we will compensate the participants accordingly according to the “Regulation on the Handling of Medical Malpractice” in China. Written informed consent is necessary from each couple as a prerequisite for the trial.

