### 2.5. Dropout and discontinuation criteria

Patients who withdraw from the study voluntarily, who experience poor compliance during the study period, or who are considered not suitable for further participation in the trial by the researcher will be removed from the RCT. The reasons include, but are not limited to the following: Participants do not take EZTG at the prescribed dosage or duration; Participants experience adverse reactions or complications related to EZTG during the study period; Participants are pregnant before IVF cycle; Participants take other medications during the study that may interfere with the study results, such as oral conceptive pills and estradiol. The concurrent use of other TCM preparations will also not be allowed.

The trial will be terminated if there are any of the following conditions: The double-blind design is accidentally disclosed or broken, leading to the failure of the trial; Existing evidence to prove no effect of the drug; The ethics committee identifies ethical issues in the experimental process; The prespecified interim analysis finds the expected difference in efficacy between the groups.

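### Section 2.12 requires a blind-break and discontinuation after a serious adverse event, with no condition of relatedness or medical need

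*Protocol article*

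**What the plan says.** The rule is in section 2.12 (Ethics and consent to participate). Adverse events are first graded: "The intensity of adverse events will be categorized as light, moderate, serious, and suspected unexpected serious adverse events". Then: "Serious adverse events should be reported to the TMC immediately". The next sentence gives the action: "Meanwhile, the blind-break process will be performed, and the trials will be discontinued". Relatedness enters only after that, and for another purpose: "If the relationship with the trial is confirmed, we will compensate the participants accordingly".

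Other sections bear on the same ground:

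- **Section 2.5** lets a participant be removed for adverse reactions or complications that are related to EZTG, within a list described as not exhaustive. Separately, under the words "The trial will be terminated if there are any of the following conditions", it lists four conditions: failure of the blind, evidence of no effect, an ethical problem, and an interim efficacy finding.
- **Section 2.6** commits to blinding of assessors and analysts ("The outcome assessment and data analysis will also be conducted in blinding") and places the last unblinding at the end: "When the clinical trial is over, the final blind-break process is performed by authorized researchers".
- **Section 2.7.1** ends study drug on the day of trigger. **Section 2.10** runs follow-up to 1 year after randomization, or to a live birth or transfer of all embryos.
- **Section 2.11** makes the TMC, which includes the principal researchers of the centers, responsible for assessing adverse events and for "the decision on terminating the study or not".

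**The concern.** The article states an action and attaches no condition to it, so this is more than detail left to a fuller document. A center that follows the sentence would break the code and discontinue the woman after any SAE, whether or not it could be related to study drug and whether or not the allocation would help anyone treat her. A hospital admission in pregnancy, months after the last dose, would qualify.

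Three things are at stake:

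- **Blinding.** Each unnecessary code-break creates a route by which allocation can reach center staff.
- **Completeness of later outcomes.** If a center takes discontinuation to mean the end of follow-up, clinical pregnancy, early miscarriage and cumulative live birth may be missing for that woman and would rest on the multiple imputation planned in section 2.9.2.
- **Clarity of stopping.** The plural noun in the sentence can be read as the whole study.

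A lesser matter is the grading scale. It is labelled as intensity but puts seriousness and expectedness on the same ladder as severity and has no severe grade, so the category that triggers the rule is loosely defined.

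**Working it through.** **1. Is the rule conditional anywhere?** The passages side by side:

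| Question | Section 2.12 | Elsewhere |
|---|---|---|
| Does removal of a woman require relatedness? | No | Section 2.5: yes, for adverse reactions and complications, but the list is open-ended |
| Is an SAE a ground for ending the trial? | Wording permits it | Section 2.5: not among the four conditions. Section 2.11: the TMC decides |
| When is the blind broken? | At the time of the SAE report | Section 2.6: the final break comes after the trial |
| Does the rule lapse when dosing ends? | Not stated | Dosing ends at trigger (2.7.1); follow-up runs to 1 year (2.10) |

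Nothing in the right-hand column narrows the rule. Sections 2.5 and 2.11 do make the participant-level reading the more likely one.

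**2. The plan's own sample size.** Inputs from section 2.9.1: difference 1 oocyte, SD 3, two-sided 5%, power 90%, dropout 20%, total 480.

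Normal approximation: n = 2 × 3² × (1.960 + 1.282)² / 1² = 189.1, so 190 per arm. Then 190 / 0.80 = 237.5, so 238 per arm and 476 in total. With the t distribution, n = 190.1, so 191 per arm; 191 / 0.80 = 238.75, so 239 per arm and 478 in total. The stated 480 is reproduced.

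**3. How many women, and what effect?** The article gives no SAE rate. I assume a risk q per woman of 0.1% to 2%, equal in both arms.

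- Women affected = 480 × q.
- Power if all were lost before retrieval *in addition to* the 20% dropout: n per arm = 240 × (1 − 0.20 − q), two-sided t-test, difference 1, SD 3.
- Width of the worst-case bounds on a between-group risk difference if a fraction q is missing in each arm: 2q. One extreme takes every missing woman in one arm as an event and none in the other; the other extreme is the reverse.

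| q | Women affected | n per arm | Power | Bound width (percentage points) |
|---|---|---|---|---|
| 0 | 0 | 192.0 | 90.3% | 0 |
| 0.1% | 0.5 | 191.8 | 90.2% | 0.2 |
| 0.5% | 2.4 | 190.8 | 90.1% | 1 |
| 1% | 4.8 | 189.6 | 89.9% | 2 |
| 2% | 9.6 | 187.2 | 89.6% | 4 |

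Both right-hand columns are upper limits. The power column probably counts the same losses twice, because discontinuations after an SAE plausibly fall within the planned 20%; in that case the extra loss is about zero. Events after retrieval cannot affect the oocyte count at all. The bound column applies only if follow-up really ends at discontinuation, which the article does not say.

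**The case against.** The best case for the plan is as follows. This is a condensed article, and code-break criteria, SAE definitions and the list of people told the allocation normally sit in the full protocol. Section 2.6 speaks of a *final* blind-break, which leaves room for individual breaks before it. Unblinding after an SAE errs toward protecting the woman. The ITT principle, the 1-year follow-up and the per-randomized definitions of clinical pregnancy and early miscarriage all suggest that she stays in the analysis. The adverse-event scale enters no planned efficacy analysis.

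Much of this stands. There is no flat contradiction with section 2.6, missing outcomes are a possibility only, and the scale is a labelling matter. What does not stand is the appeal to condensation: the article states the action, and a fuller document that restricted it would have to overrule this sentence.

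Three stronger readings are tempting, and the document does not support them:

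- *The first SAE stops the trial.* Taken so, the chance of a stop would be 1 − (1 − q)^480: 38% at 0.1%, 91% at 0.5% and 99.2% at 1%. Sections 2.5 and 2.11 point the other way, so these figures show only why the ambiguity should be removed.
- *The affected women's remaining outcomes will be assessed unblinded.* No section says that assessors learn the allocation. The risk is leakage: the TMC receives the SAE report and includes the center principal researchers. The later outcomes concerned (a gestational sac on ultrasound, pregnancy loss, live birth) leave little room for judgement.
- *The trial loses meaningful power.* It does not, as the table shows.

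**Conclusion.** The concern holds as a defect of wording with a small expected effect. Section 2.12 fixes an unconditional blind-break and discontinuation after an SAE, no other section limits it, and section 2.5 applies a relatedness standard to adverse reactions that section 2.12 drops. Followed literally, it unblinds and discontinues women for unrelated events and for events long after dosing, when the allocation may serve no purpose in their care.

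The consequences are a risk to blinding through the TMC and, if discontinuation is applied as end of follow-up, missing pregnancy and live-birth outcomes in a handful of women. The size rests on an assumed SAE risk and on equal risk in the arms. The primary outcome and power are essentially untouched. The point deserves correction for the sake of safety procedure and internal consistency, not because it threatens the main result. Confidence is medium, because the operative sentence is ambiguous and the full protocol is not shown.

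**What to change.** Reword section 2.12 along these lines:

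1. An individual code is broken only when the allocation is needed for the woman's care or for safety reporting. The allocation goes only to those who need it, and outcome assessors stay blinded.
2. Study drug is stopped for that woman only where clinically indicated. She remains in ITT follow-up to 1 year.
3. Termination of the whole trial is a decision of the TMC, consistent with sections 2.5 and 2.11.
4. As a minor correction, record severity (mild, moderate, severe) separately from seriousness, relatedness and expectedness.

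The cost is protocol and case report form wording. Sample size, visits and analysis do not change.
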